### Resources

The RCT relies on human resources and materials available in the INTRAS Foundation memory clinics in Zamora and Valladolid, Spain, and is supported by the Department of Innovation at the Iberian Institute of Research in Psychosciences (IBIP) in Zamora, Spain and the Department of Development at the INTRAS Foundation in Valladolid, Spain. The IBIP provides access to neuropsychological tests, infrastructure, materials and computers, which are necessary for conducting the study.

The centres involved in the study which do not belong to INTRAS Foundation will independently provide materials and human resources necessary for the study. The INTRAS Foundation will provide the centres with the GRADIOR software, access to ehcoBUTLER platform, training of the interviewers and supervision during the interventions to register any incidents or potential problems.

The other collaborating centres are the University of Salamanca, the Study Institute of Health Sciences of Castile and Leon health system (IECSCYL) and the Psychiatry Services and Mental Health Department of the Care Services in Zamora, Spain.

### Ethical approval

The protocol was submitted for ethical approval in May 2017 to the Zamora Provincial Hospital Ethics Committee and the trial was registered with ISRCTN with a reference number 15742788. Ethical approval was obtained on 17 May 2017. All participants will obtain written informed consent about their rights to access the information, data modification, elimination or correction following the Ley 11/1999 for data protection. All participants will sign the informed consent form at the beginning of the study and before any procedure is conducted.

Up until now, no adverse effects of GRADIOR or ehcoBUTLER have been reported and there are no known side-effects related to the usage of these programmes. Should any adverse effects be reported during the conduct of the study, they will be recorded by the staff member involved and the appropriate study coordinator will be informed.

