#### GRADIOR: Computer-based cognitive rehabilitation (GRA)

GRADIOR is a neuropsychological rehabilitation programme activating seven areas of cognitive functions (memory, attention, orientation, perception, calculus, executive functioning and reasoning) with specific tasks. In total, GRADIOR contains 48 different types of exercises with 2 to 11 levels of difficulty (see Appendix). For every participant, the GRADIOR treatment will include exercises for all cognitive subdomains. At the starting point of the treatment, all the participants will receive the same set of exercises which will differ in the level of difficulty for every subdomain based on the participant’s performance in the preliminary baseline treatment.

Participants will attend treatment sessions three to four times per week for 30 min per session. The days or distribution of treatment sessions during the week will depend on the availability of each centre and on the individual availability of participants. The treatment for each participant will be adjusted after 4 months when a midterm assessment will take place. The treatment can also potentially be adjusted before this time based on the participant’s performance in the exercises.

Every exercise in GRADIOR has a duration of 1 min during which different stimuli are presented to the participant who is then asked to provide a specific response (e.g. point only to a certain group of objects). During one treatment session, the exercises are randomised for each subdomain; however, the order of the subdomains in the treatment is fixed. If the participant does not complete all exercises on the list in one session, the subsequent session will pick up from where they stopped, i.e. with tasks for subdomains which are next on the list. In this way, the programme continues in a loop. The user does not repeat the same exercises every session, but only once they have finished the previous set.

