#### ehcoBUTLER: Computer-based psychosocial stimulation (PSS)

EhcoBUTLER is an e-health platform available via the Internet, which aims to promote physical and mental health, social participation, quality of life and personal wellbeing. EhcoBUTLER is aimed at people with MCI or mild dementia as well as their carers.

During the first two sessions participants will be trained to use the system, after which they will use the platform for 5 h per week or more. The time schedule of usage of the platform will depend on each participant and their needs and individual availability. It will be recommended to participants that they use the platform for 2 h per day. To ensure correct usage of the platform, the sessions taking place outside of the participants’ homes will be facilitated by a member of staff. Study coordinators will have access to the data registered by the platform to ensure the participation of all users. On the other hand, the therapist may use the ‘Task List’ function to propose activities to the participants and subsequently monitor their accomplishments.

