#### ehcoBUTLER CARE: Combined treatment (GRADIOR + psychosocial stimulation) (COM)

The group receiving both cognitive rehabilitation and the psychosocial stimulation treatment will have scheduled sessions with GRADIOR twice per week for 30 min per session and will be advised to use ehcoBUTLER for at least 3 h per week. The treatment sessions with GRADIOR will be the same as the group only using GRADIOR and the same procedure will be followed to determine the baseline, adjustments of treatments and levels of difficulty.

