### Treatment adherence

Interviewers will be trained clinical psychologists or neuropsychologists. All interviewers and staff included in the study will be provided with a set of guidelines for communication with participants to ensure that they have a correct understanding of the treatment sessions and that effective communication is established between participants and all staff members. During all GRADIOR treatment sessions, a member of staff will be present to provide support to participants, enabling their full participation in the treatment. However, the member of staff will not interfere with the treatment. All participants will be given contact details and times when they can contact study coordinators regarding any difficulties experienced or if questions arise during the treatment.

The sessions for both groups receiving cognitive rehabilitation treatment (GRADIOR and ehcoBUTLER CARE or combined treatment) will be managed by two study coordinators independently in each group to avoid personal bias. The treatment coordinators are trained in advanced in how to use the GRADIOR programme, including setting up and adjusting treatments, and also have a degree in psychology. Participants receiving treatment in a group setting will be supported during each session by a separate staff member independent from the treatment coordinators.

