Clock Drawing Test		10		X		X				X	X	X
Pattern recognition test		5		X		X				X	X	X
ADL/iADL (InterRAI HC)	Interviewer	N/A		X		X				X	X	X
Quality of life	Interviewer	20										
EQ5D-5 L		5		X		X				X	X	X
LSNS (Luben)		15		X		X				X	X	X
Mood	Interviewer	15										
GDS		15		X		X				X	X	X
Patient-carer relationship		N/A										
QCPR				X		X				X	X	X
Technological assessment	Interviewer	N/A										
ETUQ				X								
Randomisation	Study coordinator	N/A		X								
Treatment (group-specific)	Study coordinator	N/A			X	X	X	X	X	X		
Termination Form	Study coordinator	N/A	As needed throughout the study									
Adverse Event Form	Study coordinator	N/A	As needed throughout the study									
Progress notes	All	N/A	X	X		X				X		
Communication log	All	N/A	Every phone or in-person contact outside of regular visit									

*ADASCog* Alzheimer’s Disease Assessment Scale – Cognitive Subscale, *ADL* activities of daily living, *CAMCog* Cambridge Cognition Examination, *EQ5d-5 L* EuroQoL 5 dimensions, 5 levels, *ETUQ* Everyday Technology Use Questionnaire, *GDS* Geriatric Depression Scale, *LSNS* Luben Social Network Scale, *MMSE* Mini Mental State Examination, *N*/*A* not applicable, *QCPR* Quality of Patient-carer Relationship, *SUS* System Usability Scale, *TMT* Trail-making test

**Table 3 Tab3:** Time schedule

Activity/month	Responsible	−3	−2	−1	0	1	2	3	4	5	6	7	8	9	10	11	12	13	14	15	16	17	18	19	20	21	22	23	24	25	26	27
Project development	Primary researchers	X	X	X																												
Ethical Committee approval	Primary researchers			X																												
Protocol preparation	Primary researchers	X	X	X																												
Usability study (US)		X	X	X	X	X	X	X	X	X	X	X	X	X	X	X	X	X														
Informed consent for US	Researchers responsible for US			X																												
Participants selection for US	Researchers responsible for US			X																												
*Focus group*	Researchers responsible for US			X																												
Users’ testing	Researchers responsible for US			X																												
Intermediate evaluation	Researchers responsible for US				X	X	X	X	X	X	X	X	X	X	X	X	X															
Incidence registration	Researchers responsible for US																	X														
Randomised controlled trial		X	X	X	X	X	X	X	X	X	X	X	X	X	X	X	X	X	X	X	X	X	X	X	X	X	X	X	X			
Interviewers’ training	Responsible for interviewers		X	X																												

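### Adverse events are collected passively while scheduled staff contact differs greatly by arm, so any arm-level counts would confound contact with treatment

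*Protocol article*

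**What the plan says.** **How harms are captured.** Ethical approval states that "there are no known side-effects related to the usage of these programmes", and then: "Should any adverse effects be reported during the conduct of the study, they will be recorded by the staff member involved". The study coordinator is then informed. In Table 2 the cognitive, quality-of-life, mood and relationship measures have fixed marks at baseline and months 4, 12, 16 and 24. The row "Adverse Event Form", assigned to the study coordinator, has none and reads "As needed throughout the study".

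**How often staff are with participants.**
- GRA: "Participants will attend treatment sessions three to four times per week for 30 min per session". Under Treatment adherence: "During all GRADIOR treatment sessions, a member of staff will be present to provide support to participants".
- COM: "scheduled sessions with GRADIOR twice per week for 30 min per session", staffed in the same way, plus ehcoBUTLER use.
- PSS: two initial training sessions. After that, only sessions outside participants' "homes will be facilitated by a member of staff".
- TAU: usual care that study staff do not influence. No trial sessions are described.
- All arms: assessments at baseline and months 4, 12, 16 and 24 (Design).

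**The concern.** When events are recorded only as they come up, the number recorded depends on how often someone is there to hear about them. Here that opportunity is tied to the randomised arm. With the same true event rate everywhere, the GRADIOR arms could show more events than PSS or TAU simply because staff see those participants several times a week. The reverse error is also possible: problems arising when ehcoBUTLER is used at home without staff could go unrecorded.

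The wording adds a second difficulty. Ethical approval speaks of adverse *effects*, straight after a sentence about effects of the two programmes. Table 2 speaks of adverse *events*. An effect implies a judgement about cause; an event does not. If the first reading is applied, a TAU participant has no programme to which an effect could be attributed, and the control arm gives no background rate.

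At stake is whether the trial's safety data can be read by arm at all. Events not asked about during the trial are hard to recover afterwards.

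**Working it through.** The plan gives no figure for this point, so there is nothing to reproduce. The check has two parts.

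**1. Scheduled staffed contact during the treatment year (52 weeks)**

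| Arm | Basis | Staffed sessions | Hours at 30 min |
|---|---|---|---|
| GRA | 3 to 4 per week, staff at all | 3 × 52 = 156 to 4 × 52 = 208 | 78 to 104 |
| COM | 2 GRADIOR sessions per week, staff at all | 2 × 52 = 104, plus any facilitated ehcoBUTLER sessions | 52, plus the same |
| PSS | 2 training sessions, then staff only outside the home | 2 plus an unstated number | not stated |
| TAU | no trial sessions | 0 | 0 |

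After baseline, the contacts common to all arms within that year are the assessments at months 4 and 12. These are counts of opportunity, not of detection.

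**2. What unequal capture could do (illustration only)**

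The true risks and capture proportions below are assumptions; none is in the document. Suppose two arms share the true risk p, and a proportion c₁ of events is captured in one and c₀ in the other. The recorded risks are p·c₁ and p·c₀, so the apparent risk ratio is c₁/c₀ whatever p is.

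The chance that a two-sided 5% test finds a difference is approximately Φ[(|p₁ − p₀| − 1.96·SE₀)/SE₁]. Here p₁ = p·c₁ and p₀ = p·c₀, SE₀ is the pooled and SE₁ the unpooled standard error. The number per arm is n = 340/4 = 85, from the 340 participants expected after 15% dropout from 400.

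| Capture c₁ vs c₀ | Recorded risks at p = 20% | Apparent ratio | Chance of a false difference |
|---|---|---|---|
| 90% vs 70% | 18% vs 14% | 1.29 | about 11% |
| 90% vs 50% | 18% vs 10% | 1.80 | about 32% |
| 90% vs 30% | 18% vs 6% | 3.00 | about 68% |

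For the middle row, SE₀ = √(2 × 0.14 × 0.86/85) = 0.0532 and SE₁ = √[(0.18 × 0.82 + 0.10 × 0.90)/85] = 0.0529. This gives Φ[(0.08 − 0.1043)/0.0529] = Φ(−0.46) ≈ 0.32.

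Over true risks of 10% to 30% and the same capture pairs, the chance runs from about 7% to about 87%. That width shows why the size of the bias cannot be stated from the document.

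**The case against.** **No such comparison is planned.** The Analysis section applies group comparisons to the outcome measures, and adverse events are not among them. A reader might infer that a planned safety analysis is biased. The document does not support that. The point concerns any arm-level counts reported later.

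**Every arm has some route.** All participants receive coordinator contact details. Table 2 has a communication log for contacts outside regular visits, and progress notes at baseline and months 4 and 12. Mood, quality of life and the carer relationship are measured in all arms on the same schedule. This stands, and it rules out saying that counts would reflect contact *instead of* treatment. These routes still do not put the same adverse-event question to everyone, and the contact route is described for difficulties or questions arising during treatment.

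**A condensed article may omit the elicitation procedure.** True, and the full protocol may contain one. The article is not merely silent, however: it prints a rule and a schedule entry, and both are passive.

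**Other inferences a reader might draw.**
- That under-detection in one arm changes which treatments are modified. Interventions – modifications links observed harms to the month-4 testing, which is the same in all arms, not to spontaneous reports.
- That the documents contradict each other on who records. Staff recording and then informing the coordinator, who completes the form, is one coherent chain. Only effects versus events remains to be reconciled.
- That blinded interviewers would learn the allocation through such reports. This is possible, but nothing in the document shows it.

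**The remedy is imperfect.** Coordinators run the GRADIOR arms and so know allocation there, and recall must span several months in people with memory impairment. Both limits are real. Fixed wording and a reference person reduce them but do not remove them.

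**Conclusion.** The point holds as a weakness in harms collection. Capture as stated is passive, and scheduled staffed contact in the treatment year runs from none in TAU, apart from assessments, to 156 to 208 sessions in GRA. Arm-level adverse-event counts obtained this way would confound contact with treatment, and unsupervised home use is where capture is thinnest.

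The contact counts rest only on the stated schedules and a 52-week year. The ratios of 1.29 to 3.00 rest on assumed capture proportions and are not estimates for this trial. The efficacy analysis and sample size are untouched, and no stated conclusion of the trial depends on an adverse-event comparison. The change is worth making because it is cheap and has to be in place before the data are collected.

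**What to change.** 1. In Table 2, give the Adverse Event Form fixed marks at months 4, 12, 16 and 24 in all four arms, and keep the as-needed entry for reports in between.
2. At those visits the study coordinator asks the participant and the reference person the same short, scripted question and records all events regardless of suspected cause. Table 2 already has the coordinator handling the consent form in those months.
3. Use one term in Ethical approval and Table 2, so that recording does not depend on a prior judgement about cause.
4. Base any summary by arm on the solicited events. List session-reported events separately, so that nothing is lost.

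The cost is one amended table row, slightly longer visits and more minor events to record. The remaining weakness is recall over intervals of 4 months (baseline to 4, 12 to 16) and 8 months (4 to 12, 16 to 24), but it applies on the same schedule in every arm.

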### Outcome measures and hypotheses

#### Primary outcome measures

GRADIOR stimulates cognitive functioning, which is reflected in changes in separate cognitive domains. Outcome measures were selected accordingly. The primary aim of the study is to determine whether the cognitive rehabilitation programme GRADIOR improves cognition of people with MCI and PwD in a specific (GRA) or combined treatment group (COM). Based on previous research in this area, and our previous experience with the GRADIOR programme in a clinical setting, we expect that the two treatment groups using GRADIOR solely and in combination (COM) will achieve significantly higher scores in cognitive testing than the TAU group after 4 and 12 months of treatment. The primary outcome measure will be an ADASCog Cognitive Subscale [36].

The change in cognitive performance after a period of 4 months and 12 months in comparison with baseline results will be measured in all study groups using the *ADASCog Cognitive Subscale* [36] as the primary outcome, which evaluates cognitive performance in memory, praxis, orientation and language. Additionally, the Spanish version of the *Mini-Mental State Examination (MMSE)*, consisting of 35 questions [37], will be used*.* For a more comprehensive evaluation of a participant’s cognitive profile, we will use a variety of tests: the *Clock Drawing Test* [38] for general cognitive and spatial functioning, *WAIS III – Coding digit symbol, Calculus and Digit Span* subtests [39] to evaluate processing speed, numeric reasoning and working memory respectively, the *Rivermead pattern recognition test* [40] for visual memory, *Trail-making tests A and B* [41] to monitor motor functioning, executive functioning and visual-spatial abilities (part A) and also sustained attention (part B), the *Cambridge Cognitive Examination (CAMCog) – matrices* subtest [42] to examine intellectual ability, analogic reasoning and abstraction capacity and *Semantic and phonologic verbal fluency* [43] and [44] on animal category and letters P, M and R.

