Computer-based cognitive interventions are a cost-effective and flexible approach which are nowadays easily accessible to the public [17]. Computer-based cognitive trainings have shown to be efficient in people with MCI, which is important when addressing Alzheimer’s disease prevention or delaying the onset of the disease [18]. Currently, the field of cognitive rehabilitation for people with MCI is relatively underdeveloped in comparison to cognitive training. However, studies have shown that computer-based cognitive rehabilitation can also improve general cognition [19], as well as reduce depression and anxiety symptoms in MCI [20]. A meta-analysis by García-Casal et al. [21] reported a significant improvement in cognition, depression and anxiety in PwD involved in computer-based cognitive interventions. Furthermore, it has been reported that computer-based cognitive rehabilitation is able to delay memory deterioration in PwD [22]. People with dementia with low levels of function can also benefit from computer-based rehabilitation programmes which can improve different cognitive domains and mood [23]. Although a different meta-analysis did not reveal any significant changes in cognition for PwD, more studies are necessary in order to discover the potential long-term effects of computer-based cognitive interventions in PwD [24].

Stimulating social activities can serve as an effective prevention strategy in primary care, delaying cognitive deterioration in older PwD and MCI [25]. Psychosocial interventions can also introduce positive changes in cognition, mood or communication in PwD [26] and MCI [27].

GRADIOR is a computer-based programme used for the neuropsychological rehabilitation of people with various cognitive impairments of different aetiology, as well as for cognitive stimulation of healthy individuals. GRADIOR consists of dynamic exercises designed to stimulate all cognitive abilities, offering tools to tailor the cognitive intervention to each person according to their individual needs. The programme also provides tools for the evaluation of the current performance in every cognitive domain, which is important for treatment adjustments (changing difficulty levels for each task independently according to the participants’ performance).

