For this reason, we will conduct an interviewer-blinded, multi-centre randomised controlled trial with four parallel groups. The primary aim of which is to determine the effectiveness of the cognitive rehabilitation programme GRADIOR and the psychosocial stimulation platform ehcoBUTLER, separately or in a combined treatment, on the cognition, quality of life, activities of daily living, relationships with carers and depressive symptoms of people with MCI and PwD. Based on previous research, we hypothesise that people with MCI and PwD in the cognitive rehabilitation group using GRADIOR or combined treatment will improve their cognition in comparison to other treatment groups and/or the treatment as usual (TAU) group. A secondary aim is to examine the interaction between psychosocial stimulation and cognitive rehabilitation in order to discover their synergies or usefulness. The duration of the RCT is 1 year of treatment followed by a 1-year follow-up study.

A preliminary study on the usability of GRADIOR and ehcoBUTLER will be conducted through focus groups and users’ testing in order to identify any issues in the programme’s features which may potentially influence its effectiveness in MCI and PwD. Additional data will be collected and any incidents will be monitored to improve the final usability of both programmes.

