Carers will also be assessed at the same time as participants, whereby we will evaluate the following: their anxiety using the *State-Trait Anxiety Inventory (STAI)* [51], symptoms of depression with the *Beck Depression Inventory II (BDI-II)* [52], carer overload using the *Caregiver Burden Interview – Zarit Test* [53] and the quality of their relationships using the *Quality of Carer-patient Relationship (QCPR*) *questionnaire* [49]. We anticipate that GRADIOR will positively influence carer-outcome measures, and therefore, we hypothesise that in both intervention groups using GRADIOR, caregiver burden, anxiety and depression will decrease, and the relationship between the carer and the PwD will improve.

The data collected from the InterRAI Home Care Assessment will be used to analyse the cost-effectiveness of the treatment and its impact on health. The economic evaluation will employ a cost-consequences framework evaluating the associated costs and outcomes of the three types of interventions, in comparison to usual care. The evaluation will also assess the main sources of costs associated with the interventions. Primary analysis will be based on the most plausible real-world costs, including the cost of the technology and technical progress. The support costs for GRADIOR and ehcoBUTLER associated with technical aspects of installation, maintenance of hardware and information, as well as communication technology input related to software and data management, will be based on data gathered from sites. This will also include the input of professionals for guiding participants and support provided to participants throughout the intervention. For a complete list of the assessment tests used and the time schedule see Tables 2 and 3 respectively.

**Table 2 Tab2:** Assessments

Activity/assessment	Staff member	Time	Pre-study	Pre-study baseline	2	4	6	8	10	12	16	24
Usability study	Interviewer	N/A	X									
Focus group		90										
SUS		N/A										
Consent Form	Study coordinator	5	X	X		X				X	X	X
Inclusion/exclusion criteria	Study coordinator	N/A	X									
DSM-5 criteria	Interviewer	N/A	X									
Cognitive assessment	Interviewer	106										
MMSE		20		X		X				X	X	X
ADASCog		40		X		X				X	X	X
WAIS III: Calculus		5		X		X				X	X	X
WAIS III: Digit Span		5		X		X				X	X	X
WAIS III: Coding digit symbol		2		X		X				X	X	X
TMT A and B		10		X		X				X	X	X
Semantic and phonologic verbal fluency		4		X		X				X	X	X
CAMCog matrices		5		X		X				X	X	X

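### The combined arm against usual care tests GRADIOR plus ehcoBUTLER, yet the primary aim lets that result stand as evidence for GRADIOR

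*Protocol article*

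**What the plan says.** All references are to the Protocol article.

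- **Primary aim** (Primary outcome measures): to find out "whether the cognitive rehabilitation programme GRADIOR improves cognition of people with MCI and PwD in a specific (GRA) or combined treatment group (COM"). The effect in question is GRADIOR's.
- **Primary expectation** (same section): after 4 and 12 months, "the two treatment groups using GRADIOR solely and in combination (COM) will achieve significantly higher scores in cognitive testing than the TAU group". TAU is the only comparator named there, and ADASCog is the primary outcome.
- **Content of COM** (section on the combined treatment): two 30-minute GRADIOR sessions a week, and participants "will be advised to use ehcoBUTLER for at least 3 h per week".
- **ehcoBUTLER and cognition** (Background): the platform is described as including cognitive training tools, and the protocol says of its class that "Psychosocial interventions can also introduce positive changes in cognition, mood or communication in PwD".
- **Other statements of aim** (Background): the primary aim there covers GRADIOR and ehcoBUTLER, each alone or combined. The hypothesis is that participants receiving GRADIOR, alone or combined, "will improve their cognition in comparison to other treatment groups and/or the treatment as usual (TAU) group". The Background adds: "A secondary aim is to examine the interaction between psychosocial stimulation and cognitive rehabilitation in order to discover their synergies or usefulness".
- **Analysis**: a repeated measures ANOVA for all outcomes, with Bonferroni or Dunnett corrections post hoc if needed.

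**The concern.** The aim asks about one programme, but one of its two comparisons changes two programmes at once. COM versus TAU can be positive because of GRADIOR, ehcoBUTLER, or both. The protocol makes the ehcoBUTLER explanation plausible by its own account. In COM the advised ehcoBUTLER time (at least 3 h a week) is at least three times the GRADIOR time (2 × 30 min = 1 h).

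At stake is the attribution of the primary claim. A multiplicity correction makes a positive COM result rarer but does not cure the problem, because the difference would be real and only its cause misnamed. The Background hypothesis does not close the gap: its *and/or* lets the TAU comparison suffice.

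**Working it through.** **1. What each contrast estimates.** Write G for the GRADIOR effect, E for the ehcoBUTLER effect and I for any interaction, with subscripts for the arm because the advised amounts differ.

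| Contrast | Estimates |
|---|---|
| GRA − TAU | G(GRA) |
| COM − TAU | G(COM) + E(COM) + I |
| COM − PSS | G(COM) + I + [E(COM) − E(PSS)] |

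Only the first is free of ehcoBUTLER. The second can be positive with G = 0 and I = 0.

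**2. Inputs and the plan's own figures (Sample size).** 400 × 0.85 = 340 reproduces. The precision figure 1.96 × 0.5 / √340 = 5.31% reproduces the stated 5.3%. The stated 80% power for an effect of about 0.30 with 340 participants reproduces if 0.30 is a standardised mean difference between two groups of 170 (power 79.0%). With 1:1:1:1 allocation there are 340 / 4 = 85 per arm. The present point does not depend on the power statement; only the 85 is used.

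**3. Chance that COM beats TAU when only ehcoBUTLER works.** Assumptions: 85 per arm, G = 0, I = 0, E(COM) = d in full, two-sided 0.05. The values of d are assumed.

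Probability = Φ(d × √(85/2) − z), with √42.5 = 6.519; z = 1.960 at 0.05 and 2.241 at 0.025.

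| d | d × 6.519 | at 0.05 | at Bonferroni 0.025 |
|---|---|---|---|
| 0.20 | 1.304 | Φ(−0.656) = 25.6% | Φ(−0.937) = 17.4% |
| 0.30 | 1.956 | Φ(−0.004) = 49.8% | Φ(−0.285) = 38.8% |

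A noncentral t calculation gives 25.3% and 49.4% at 0.05. If ehcoBUTLER acts in COM at only 60% of d (3 h of 5 h, assuming linearity), the same method gives 11.9% and 21.4%.

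**4. Effect of the success rule.** Simulation under the assumptions of step 3 (400,000 runs, unadjusted 0.05):

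| Rule for claiming GRADIOR works | d = 0.20 | d = 0.30 |
|---|---|---|
| GRA or COM beats TAU | 26.3% | 50.1% |
| GRA and COM both beat TAU | 1.8% | 2.3% |
| GRA beats TAU | 2.5% | 2.5% |
| COM beats PSS, equal ehcoBUTLER effect in both arms | 2.5% | 2.5% |

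**5. COM versus PSS is not clean.** ehcoBUTLER is set at 5 h a week or more in PSS and advised for at least 3 h in COM. If the effect scales with time, E(COM) − E(PSS) = 0.6d − d = −0.4d, that is −0.08 at d = 0.20 and −0.12 at d = 0.30, against GRADIOR. COM is also labelled ehcoBUTLER CARE. The Background says the care version adds activities, and the version used in PSS is not stated.

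**The case against.** The strongest reply is that the expectation names GRA *and* COM. If both must beat TAU, GRA versus TAU guards the claim and a false GRADIOR conclusion stays at or below 2.5%. The *or* in the aim may merely list the two settings in which GRADIOR is given. This stands as a fair reading: the text is an expectation, not a formal decision rule. It does not settle the matter, because the aim sentence permits the other reading and nothing in the article excludes it.

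Second, the Background frames the combination as a treatment in its own right, and COM versus TAU suits that question. This also stands. It shows that the two statements of the aim need reconciling, not that the GRADIOR wording is sound.

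Third, all four arms are measured, comparison with other arms is allowed and the interaction is a secondary aim, so a pattern of PSS and COM above GRA and TAU would be visible. The design can therefore answer the question; the primary expectation just does not use the arm that would help. Detailed contrasts may be in an analysis plan not shown. The point here is what the article does state: a GRADIOR aim paired with a package comparison.

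Two stronger inferences should be resisted. A reader might conclude that the trial *will* misattribute an ehcoBUTLER effect. The documents support only that it *could*, under the *or* reading. A reader might also extend the criticism to carers, where the protocol predicts that "in both intervention groups using GRADIOR, caregiver burden, anxiety and depression will decrease". That hypothesis covers both GRADIOR groups and names no TAU contrast, so the same fault is not shown.

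**Conclusion.** The point holds in a limited form. COM versus TAU cannot by itself support a statement about GRADIOR, and the primary aim as worded allows it to be used that way. GRA versus TAU is unaffected.

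The percentages are illustrations. They assume no GRADIOR effect at all, full ehcoBUTLER action in COM and an effect size that the protocol does not give. They shrink with partial delivery or a multiplicity correction, and the false-claim risk largely disappears if both comparisons must succeed. This is a fault of wording and attribution in the primary claim, not of the design or the data to be collected.

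**What to change.** In Primary outcome measures:

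1. Make GRA versus TAU the ADASCog test of the GRADIOR claim.
2. Keep COM versus TAU, described as a test of the GRADIOR and ehcoBUTLER package that cannot by itself support a statement about GRADIOR.
3. Rest any statement about GRADIOR's added effect within the combination on COM versus PSS. State that ehcoBUTLER time, and possibly version, differs between these arms, so the contrast may be biased against GRADIOR.
4. Reconcile this wording with the Background, where the combination is treated as a package.

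The cost is protocol and analysis plan wording plus one contrast between existing arms, with no new data. The downside is that the GRADIOR claim becomes harder to support from the combined arm. The change should be made before unblinded results are seen.
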